## Methods/design

### Aims and hypothesis

The main aim of the DeTaMAKS study, which began in October 2014, is to assess whether a combined intervention can promote and sustain abilities to perform ADL and cognitive capacities and thus independence in people with MCI or mild or moderate dementia, which should also provide some relief for the informal caregiver.

There is also the hope that combining the MAKS therapy in day-care centres with a brief telephone intervention for informal caregivers will make it easier for the caregivers to reconcile the home care they are providing with their work, thus delaying the transition to institutional care and decreasing the costs for the healthcare system.

Research hypotheses:i.The MAKS therapy leads to a statistically significantly greater improvement in abilities to perform ADL and cognitive capacities over time in people with MCI and dementia as compared with “care as usual” in the control group.
ii.The combination of MAKS therapy and brief telephone interventions for informal caregivers leads to statistically significantly more favourable subjective perceptions of burden and well-being in informal caregivers than in the control group.
iii.The interventions lead people with cognitive impairment to remain in home care for longer after the 2-year period of data collection and thus result in an economic health advantage over the control group.

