#### Implementation of the MAKS therapy in the DeTaMAKS project

The day-care centres in the intervention group committed themselves to carrying out the therapy in accordance with the manual every morning from Monday to Friday for 6 months. On each day of the therapy, all study participants attending the day-care centre on that day take part in the MAKS therapy. This results in average “doses of therapy” of one to five therapy days per week. The MAKS therapy is carried out by no less than two trained therapists. At least one of the two therapists is a qualified healthcare professional (geriatric nurse, nurse, or occupational therapist). The one-day training event for the staff of the day-care centres and the material used in the therapy were given to the day-care centres in the intervention group at baseline and will be given to the centres in the control group 6 months later. Study headquarters’ staff members are available to answer questions by phone or by e-mail on all weekdays.

The project does not exert any influence on the usual services of any of the 34 day-care centres, the pharmacotherapy of the study participants, or the frequency of attendance. Day-care users were free to choose their day-care centre and were free to decide whether to participate in the MAKS therapy. However, all changes in the frequency of attendance of the day-care centre are documented for all study participants.

A precursor to the intervention was implemented in nursing homes in a randomised-controlled trial [15] to record serious adverse events (falls resulting in injury, other types of serious injury and deaths), which did not increase over a period of 12 months. This is why we forwent the recording of serious adverse events (except death) and why no stopping guidelines were necessary. For this reason, we expect that the benefits of the MAKS therapy will far outweigh any possible harm. Also, because the intervention was implemented within the care of the day-care centres, participants did not need additional accident insurance.

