*Changes in the day-care centre situation (monthly)*. During the 6-month intervention phase, we kept track of the presence of the study participants. Specifically, we recorded periods of and reasons for extended absences (longer than 1 week), changes in the level of care, and whether the participants left the day-care centre (terminated the contract, moved to a nursing home, died) or the project (withdrew consent). These data were tracked daily and reported monthly.

*Evaluation of the MAKS therapy.* The MAKS therapists in the day-care centres in the intervention group documented the attendance of the study participants and any deviations from the manualised procedure on each day of therapy of the 6-month intervention period in order to monitor the intensity and quality of the MAKS therapy. After the end of the 6-month intervention period, the therapists at the day-care centres attended by the intervention group participants were also asked to submit their subjective assessments of the 3 most suitable and 3 least suitable tasks in each MAKS component. In addition, from the follow-up survey conducted after 6 months and onwards, the informal caregivers in both arms of the study were asked to rate potential changes in the care recipients’ alertness/activity, initiation of contact/talkativeness, physical mobility, mood, and thinking/memorising capacities on a 3-point scale (improved/remained the same/worse). They were also asked about the occurrence of three types of severe adverse events (falls resulting in injury, other injuries requiring medical treatment, and other serious adverse events).

In order to obtain information on the sustainability of the MAKS therapy 12 and 24 months after baseline, the day-care centres are asked how they are carrying out the MAKS treatment after the end of the 6-month intervention phase.

*Evaluation of the brief telephone intervention for informal caregivers.* After the end of the 6-month intervention phase, the caregivers in the intervention group were asked to evaluate the brief telephone intervention. The questionnaire contained 4 questions that pertained to satisfaction with the intervention (example: “I learned from the counselling how I can pay better attention to my own needs”) that were rated on a 3-point scale (“I totally agree”, “partly yes, partly no”, “I don’t agree at all”). They were also asked about qualitative aspects (“What did you like?”, “What did you dislike?”).

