### Analysis

#### Data analysis

Only researchers at the study centre in collaboration with the Institute of Health Economics and Health Care Management will assess the results. Our cooperation partner will check the plausibility of the data independently. Thus, there is no need for a data monitoring committee.

The data analyses will be performed with the aid of the “IBM SPSS Statistics 21” software.

If at least 80% of the items on a test have been answered, we will impute missing values from the mean score of the existing items. However, if more than 20% of the items on a test are missing for any given person (e.g. because a participant refuses to complete the test), we will compute the score according to the expectation maximum (EM) algorithm, which uses the variables that explain the greatest proportion of variance in the missing variable.

All changes to the data due to checking for errors, data quality management, or the handling of missing values will be documented.

In order to be able to assess the quality of the randomisation, the baseline data from the intervention and control groups will be examined for statistically significant differences.

The two hypotheses on the efficacy of the interventions in people with cognitive impairment and their caregivers will be tested by computing multiple regression analyses. The transition to institutionalised care as an event will be represented by a Kaplan-Meier curve for the intervention and control groups. The hypothesis on the transition to institutionalised care will be evaluated by Cox regression analysis.

As the primary outcome variables cannot be tested at follow-up in participants who dropped out of the study, the primary data analysis strategy will be “as treated”. The level of statistical significance will be set at *p* = 0.05. Results with an alpha error of less than 10% will be classified as statistical trends.

Subgroups will also be analysed exploratively, sub-divided in accordance with the severity of cognitive impairment and the mean frequency of attendance at the day-care centre per week.

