#### Economic evaluation/ analysis

The valuation of resource use will be based on the valuation rates by Bock et al. [49]. The costs of the intervention include the training time and supervision of day-care centre staff, and materials (manuals, handbooks, etc.)., To analyse cost difference between groups, a multivariable model with a gamma distribution will be used to account for the skewed distribution of the data [50], adjusted for baseline costs. A 95-% confidence interval for the adjusted cost difference will be estimated from 1000 bootstrap replications. A cost-utility analysis from a societal perspective will be performed in which the quality of life of both day-care users and informal caregivers will be assessed. To calculate the quality-adjusted life years for day-care users regarding the time remaining at home, the quality of life values will be set to 0 from the day of admission to a nursing home or death. Moreover, a budget impact analysis will be computed to address changes in the expenses of the health care system if the MAKS therapy shows significant effects.

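### Admission-only Kaplan-Meier and Cox analyses censor deaths implicitly, so the curve overstates admission and the hazard ratio alone cannot show longer time in home care

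*Protocol article*

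**What the plan says.** Under Aims and hypothesis, the third hypothesis reads: "The interventions lead people with cognitive impairment to remain in home care for longer after the 2-year period of data collection". It goes on to infer an economic advantage. The paragraph before it also expresses the hope of delaying the move to institutional care.

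The Data analysis section gives the clinical analysis: "The transition to institutionalised care as an event will be represented by a Kaplan-Meier curve for the intervention and control groups", followed by "The hypothesis on the transition to institutionalised care will be evaluated by Cox regression analysis". It mentions neither a composite with death nor a competing-risk method.

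The Economic evaluation/ analysis section treats the end of time at home differently. For quality-adjusted life years relating to time at home, "the quality of life values will be set to 0 from the day of admission to a nursing home or death".

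Death is recorded. Under Other measures, the monthly reports during the 6-month intervention phase show "whether the participants left the day-care centre (terminated the contract, moved to a nursing home, died) or the project (withdrew consent"). The section on implementing the MAKS therapy names death as the one exception to not recording serious adverse events: "This is why we forwent the recording of serious adverse events (except death"). Observation lasts two years, with caregiver interviews at baseline and at 6, 12 and 24 months.

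**The concern.** Home care can end by admission or by death. The hypothesis is about how long it lasts, and the economic section accepts both endings. The clinical analysis counts one of them. The word censored does not appear in the article, but with one event type an ordinary Kaplan-Meier or Cox analysis has no other place for a person who dies at home.

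Two things are at stake. First, a reader will naturally take 1 minus Kaplan-Meier as the share of each arm admitted, and it is larger than that share whenever deaths are censored. Second, a lower admission hazard could be reported as support for hypothesis iii although participants did not spend longer alive at home. Equally, a hazard ratio of 1.00 could hide a difference in time at home.

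**Working it through.** **What the plan offers to reproduce.** It gives no event rate, event count or power for this endpoint. Its only sample-size arithmetic, 270/(1 − 0.22) = 346, concerns the primary outcome and does not bear on this point. All rates below are therefore assumptions, with hazards constant over T = 2 years: *a* for admission and *d* for death, per year.

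**Formulas.**
- 1 − KM with deaths censored: 1 − exp(−aT)
- Actual proportion admitted (cumulative incidence): a/(a+d) × [1 − exp(−(a+d)T)]
- Alive at home at T: exp(−(a+d)T)
- Mean months alive at home up to T: 12 × [1 − exp(−(a+d)T)]/(a+d)

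**Step 1: the curve.** With a = 0.15, 1 − KM = 1 − exp(−0.30) = 25.9%, whatever the mortality.

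| d | Proportion admitted | Excess of 1 − KM (points) |
|---|---|---|
| 0.05 | 0.15/0.20 × (1 − e^−0.40) = 24.7% | 1.2 |
| 0.10 | 0.15/0.25 × (1 − e^−0.50) = 23.6% | 2.3 |
| 0.20 | 0.15/0.35 × (1 − e^−0.70) = 21.6% | 4.3 |
| 0.30 | 0.15/0.45 × (1 − e^−0.90) = 19.8% | 6.1 |

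Over a = 0.10 to 0.20 and the same range of d, the excess runs from 0.8 points (18.1% against 17.3%) to 7.7 points (33.0% against 25.3%).

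The same check can start from assumed final proportions. With 30% admitted and 20% dead, the total cumulative hazard is −ln(0.50) = 0.693. The admission share is 0.693 × 0.6 = 0.416, so 1 − KM = 34% against a true 30%. With 20% and 10% the result is 21% against 20%. With 30% and 25% it is 35% against 30%.

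**Step 2: different mortality, same admission hazard, independent risks.** Take a = 0.15 in both arms, and d = 0.20 in one and 0.10 in the other.
- Admission hazard ratio: 0.15/0.15 = 1.00.
- Alive at home at two years: e^−0.70 = 49.7% against e^−0.50 = 60.7%.
- Mean time alive at home: 17.3 against 18.9 months.
- Hazard ratio for admission or death: 0.35/0.25 = 1.40.

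**Step 3: equal time at home, different admission hazards.** Suppose 30% admitted and 15% dead in control, and 20% admitted and 25% dead in intervention. Both arms have 45% out of home care, a total hazard of −ln(0.55) = 0.598 over the period, and identical time at home.
- Admission: 0.598 × 20/45 = 0.266 against 0.598 × 30/45 = 0.399, ratio 0.67.
- Death: 0.598 × 25/45 = 0.332 against 0.598 × 15/45 = 0.199, ratio 1.67.

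The 0.67 is a genuine reduction in the admission hazard, correctly estimated. It is not evidence of longer home care, because the assumed 67% higher death hazard offsets it.

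**Step 4: the same people at risk of both events.** A simulation with a gamma frailty shared by admission and death used a = 0.15 and one million people per arm.

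| Death hazards | Frailty variance | Admission HR | Admission-or-death HR |
|---|---|---|---|
| 0.20 v 0.10 | 0.5 / 1 / 2 | 0.97 / 0.94 / 0.90 | 1.35 / 1.32 / 1.27 |
| 0.30 v 0.10 | 0.5 / 1 / 2 | 0.94 / 0.89 / 0.83 | 1.68 / 1.60 / 1.50 |

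Here the arm with more deaths has the lower admission hazard ratio, but only because frailty is assumed to be shared.

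**The case against.** A fair opponent would make five points.

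1. *Admission alone is a legitimate target.* The aims include delaying institutional care, and a Cox model with deaths censored is a valid cause-specific analysis of that. This stands, and it is why the Cox model should stay. It does not extend to the wording of hypothesis iii, which concerns duration of home care.

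2. *Deaths do not flatter an arm by themselves.* A reader might infer that an arm with more deaths will look better at keeping people at home. The documents do not support that. Under independent risks extra deaths leave the admission hazard ratio at 1.00. It falls below 1 only with a real reduction in the admission hazard (step 3) or an added shared-frailty assumption (step 4).

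3. *A mortality difference is not expected.* The protocol reports that serious adverse events, including deaths, did not increase in the precursor trial over 12 months. This makes large imbalances less likely. It does not affect the curve, which is too high in both arms even at equal mortality, though by a similar amount in each.

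4. *A quality-of-life value of zero after death is standard in any such calculation.* True, but the section applies the same zero from nursing-home admission and does so for time at home. It thereby uses a death-inclusive definition that the clinical analysis lacks.

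5. *Censoring rules belong in an analysis plan that is not shown, and this is a condensed article.* Silence on censoring is indeed no finding. The event and both methods, however, are fixed in this document, and the point rests on those.

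**Conclusion.** The point holds in a limited form. The clinical analysis answers whether the hazard of admission differs. Hypothesis iii asks whether people stay in home care longer, and the economic section measures that with death included. Followed as written, the Kaplan-Meier curve would overstate the proportion admitted by roughly 1 to 8 points at two years. The admission hazard ratio could be 1.00 or lower while time alive at home is equal or shorter.

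The size depends on assumed constant hazards of 0.10 to 0.20 per year for admission and 0.05 to 0.30 for death. The divergence between hazard ratio and time at home also needs mortality to differ between arms. That deaths would be censored is inferred from the event definition and methods. It would go too far to call the Cox analysis invalid, or to say that a misleading result is likely. Hypothesis iii is outside the listed primary outcomes, so the consequence is confined to what may be claimed about home care.

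**What to change.** - Keep the Cox model for admission and label it the cause-specific analysis of delayed transition to institutional care.
- Replace the Kaplan-Meier admission curve with the cumulative incidence of admission, death being a competing event, and report deaths by arm.
- Base any statement about longer home care on time to admission or death, whichever comes first. Kaplan-Meier and Cox methods suit this endpoint. Use the same definition and dates as the economic evaluation.

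The cost is mainly wording. The composite may dilute an effect on admission, since it includes deaths that the intervention is not expected to prevent; the separate admission analysis is kept for that reason. Cumulative incidence may need an add-on to the named software. The monthly tracking of moves and deaths covers only the 6-month intervention phase, so later dates must come from the sources that the economic analysis already needs, and the plan should name them.

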### Study design and setting

A cluster-randomised, controlled, multicentre, prospective longitudinal study with a waitlist control group design was conducted to test the above research hypotheses.

All day-care centres participating in the study (cluster) were randomly assigned to the intervention or control group at baseline (random selection). The cluster was stratified by region (the Northeast, the Southeast, and the West). In order to guarantee that the sequence would be concealed until the intervention and control groups were assigned, all day-care centre staff were trained on the study protocol, instruments, and screening before the randomisation. The informed consent of the day-care users and their caregivers were also collected before the randomisation (see Fig. 1). Day-care centres were informed of their group allocation in written form by the study headquarters. During the 6-month intervention phase, the day-care centres in the intervention group carry out the MAKS treatment after their staff receive training. The caregivers receive a brief telephone intervention by counsellors with training in psychotherapy. The day-care centres in the control group do not carry out any additional project-specific treatment but continue providing “care as usual”. This is the accepted standard of care in day-care centres. Because we are investigating a non-pharmacological intervention, neither the staff carrying out the MAKS therapy nor the people with cognitive impairment are blinded. Six months after baseline, the day-care centres’ staff in the control group will also undergo training in MAKS therapy. At the end of the 6-month intervention phase, the day-care centres in both the intervention and control groups will freely decide whether or not to continue the MAKS treatment or to introduce the treatment, respectively, including the level of intensity. The observation period is 2 years with a total of four measurement points (baseline and after 6, 12, and 24 months). Data are collected by means of psychometric tests, the day-care centres’ documentation, and computer-assisted telephone interviews (CATIs) with the caregivers. All procedures were approved by the Friedrich Alexander University Erlangen-Nuremberg Ethics Committee. The external GKV Spitzenverband was closely informed of the progress of the study and achieved milestones as determined in the trial application. The study design is presented in Fig. 1. In the case of important protocol modifications, we will inform the Ethics Committee, the funders, the day-care centres, and the platform for the trial registry. Trial registration data are presented in Table 1.

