
**Fig. 1 Fig1:**
[figure not shown]
Study Design

**Table 1 Tab1:** Trial registration data

Data category	Information
1. Primary registry and trial identification number	ISRCTN16412551
2. Date of registration in primary registry	30 July 2014
3. Secondary identifying numbers	GKV-SV201
4. Source(s) of monetary or material support	Long-Term Care Insurance Funds (GKV-Spitzenverband), German National Association of the Statutory Health Insurance and
5. Primary sponsor	Long-Term Care Insurance Funds (GKV-Spitzenverband), German National Association of the Statutory Health Insurance and
6. Secondary sponsor(s)	-
7. Contact for public queries	See point 8
8. Contact for scientific queries	[name]. [name], [contact] PD [name], [contact]
9. Public title	The German Day-Care Study
10. Scientific title	Multimodal non-drug therapy for persons with cognitive decline in day-care institutions with short-term interventions for informal caregivers by telephone to strengthen the compatibility of care and work
11. Countries of recruitment	Germany
12. Health condition(s) or problem(s) studied	Mild cognitive impairment, mild or moderate dementia (degenerative type, not solely vascular)
13. Intervention(s)	Intervention group: Activation therapy for day-care users with cognitive impairment
	Control group: usual care offered in each day care (treatment as usual)
	Informal caregiver: telephone intervention
14. Key inclusion and exclusion criteria	Ages eligible for study: adults; Sexes eligible for study: both
	Inclusion criteria:
	1. Users of day-care centres with mild cognitive impairment or early dementia who have an informal caregiver
	2. Informed consent
	Exclusion criteria:
	1. Completely blind or deaf
	2. No informal caregiver at all
	3. Severe dementia
	4. Cognitive decline due to diseases other than dementia (e.g. schizophrenia or Korsakov)
15. Study type	Cluster-randomised controlled intervention study
16. Date of first enrolment	October 2014
17. Target sample size	350
18. Recruitment status	Complete
19. Primary outcome(s)	Users of day-care centres: cognition (MMSE), activities of daily living (ETAM)
	Caregivers: subjective burden (HPS-K), well-being (WHO-5)
20. Key secondary outcomes	Users of day-care centres: e.g. NPI-Q, EQ-5D
	Caregivers: EQ-5D, BIZA-D

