### Data collection

Data collection for the primary outcome variables pertaining to the people with cognitive impairment was conducted at the day-care centres by staff who were trained by the study headquarters staff. Data are collected at the beginning of the study, after the end of the 6-month intervention period, and after 12 months. To reduce the risk of investigator bias, the testers are not involved in the care of the day-care centre users.

The CATIs are administered to the caregivers by trained interviewers at the beginning of the study and after 6, 12, and 24 months in order to collect data on variables related to the caregivers’ situations (self-rating), the day-care users’ situations (observer rating), and the care situation. The procedure of CATI is described in detail by Holle et al. [48]. A short form of the questionnaire is sent to the caregivers to prepare them for the interview. All the other data mentioned in the previous section are collected by trained day-care centre staff in a standardised, written form.

The final data set consists of data collected at the day-care centres and via CATIs. The data from the day-care centres exist in written form sent to the study headquarters and are later imported electronically. The CATI data are collected and stored electronically. Some of the outcome measures (e.g. care level) are collected in both ways.

Because data collection for the primary outcome variables is conducted at the day-care centres, follow-up data on drop-outs due to death or transfer to a nursing home cannot be collected. If caregivers cannot be reached by telephone for the CATI after three tries, they are sent the questionnaires by mail with the request to mail the questionnaires back.

A pseudonym is created for the electronic data, and it cannot be used for user identification. Only the key file contains information about a person’s identity and pseudonym. All of the data (including written documents, key files, etc.) are kept securely in a locked file, and only the researchers have access to the data.

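### The primary analysis is labelled as treated, with no analysis by randomised arm named for the primary outcomes; the drop-out reason does not support this and does not reach the caregiver outcomes

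*Protocol article*

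**What the plan says.** The protocol article randomises centres: "All day-care centres participating in the study (cluster) were randomly assigned to the intervention or control group at baseline" (Study design and setting). For the primary analysis, the Data analysis section gives a reason, "As the primary outcome variables cannot be tested at follow-up in participants who dropped out of the study", and from it concludes that "the primary data analysis strategy will be “as treated". The term appears once and is not defined. No intention-to-treat or as-randomised analysis of the primary outcomes is named.

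The Data collection section explains the reason. ETAM and MMSE are tested at the centres, so "follow-up data on drop-outs due to death or transfer to a nursing home cannot be collected". The two caregiver primaries, BSFC-s and WHO-5, take another route. Caregivers are interviewed by telephone at baseline and at 6, 12 and 24 months, and "If caregivers cannot be reached by telephone for the CATI after three tries, they are sent the questionnaires by mail".

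On receipt of treatment, the section on implementing MAKS says that users "were free to decide whether to participate in the MAKS therapy".

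**The concern.** Randomising centres makes the arms comparable in expectation. Whether a user then takes part in MAKS is decided afterwards, by that user. An analysis grouped by participation compares choosers with a mixture of non-choosers and controls, and randomisation does not protect that comparison. Willingness to join a two-hour group session could well depend on cognition, mood or frailty, which could also affect later ETAM and MMSE scores.

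The stated reason does not lead to the chosen strategy. That some people have no follow-up score says nothing about the arm in which people who do have one belong. The reason also concerns testing at the centre, so it has no bearing on outcomes taken from caregivers by telephone or post. As the sentence sets the strategy for the primary outcomes without distinguishing user from caregiver outcomes, every primary conclusion depends on it.

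**Working it through.** **Reason against data source**

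| Primary outcome | Source | Needs the user at the centre? | Drop-out reason applies? |
|---|---|---|---|
| ETAM, MMSE | Test at the centre | Yes | Yes, as missing data |
| BSFC-s, WHO-5 | Caregiver, telephone with postal fallback | No | No |

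A user who declines MAKS but still attends can be tested at 6 months, so the reason does not cover that user either. The Data analysis section already has an EM step for people with more than 20% of a test's items missing, so the plan elsewhere treats missing scores as a missing-data matter.

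**Size of the loss**

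The sample size section needs about 270 people at 6 months and assumes 22% fluctuation. 270 / (1 − 0.22) = 346.15, which reproduces the stated 346. The expected loss is 0.22 × 346 = 76 people as planned, or 0.22 × 453 = 100 of the dyads actually included.

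**Illustration of the bias**

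Assumptions, none taken from the document: no true effect; n = 135 per arm (270 / 2); within-group SD of 1; no covariates; clustering ignored; a proportion p of intervention users decline MAKS and do d SD worse than takers whatever they receive. The control arm contains the same mixture, so its mean is set to 0. Takers then average +pd and decliners −(1 − p)d.

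- Decliners excluded: bias = pd, SE = √[1/(n(1 − p)) + 1/n].
- Decliners counted as untreated: the enlarged untreated group averages −p(1 − p)d/(1 + p), so bias = pd + p(1 − p)d/(1 + p), SE = √[1/(n(1 − p)) + 1/(n(1 + p))].
- Two-sided type I error = Φ(bias/SE − 1.96) + Φ(−bias/SE − 1.96).

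Worked case, p = 0.10 and d = 0.5: there are 121.5 takers and 13.5 decliners. Regrouped, the bias is 0.050 + 0.041 = 0.091, the SE is √(1/121.5 + 1/148.5) = 0.122, and the type I error is 11.5%.

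| p | d | Excluded: bias, type I | Regrouped: bias, type I |
|---|---|---|---|
| 2% | 0.5 | 0.010 SD, 5.1% | 0.020 SD, 5.3% |
| 5% | 0.3 | 0.015 SD, 5.2% | 0.029 SD, 5.6% |
| 10% | 0.25 | 0.025 SD, 5.5% | 0.045 SD, 6.6% |
| 10% | 0.5 | 0.050 SD, 6.9% | 0.091 SD, 11.5% |
| 20% | 0.5 | 0.100 SD, 12.1% | 0.167 SD, 26.9% |

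For scale, the planning effect f² = 0.06, read as a difference between two equal groups, is 2 × √0.06 = 0.49 SD. A larger sample raises the inflation: with 453 × 0.78 / 2 ≈ 177 per arm, the 10% and 0.5 SD regrouped case rises from 11.5% to 13.6%.

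The table covers decliners only. Bias from the 22% loss would depend on how losses differ between arms, on which the document gives nothing.

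**The case against.** The best defence is that the authors probably mean something milder than the label. The sentence ties the term to people who cannot be tested, the sample size counts people still attending at 6 months, and the hypotheses compare with the control group. All of this fits an available-case analysis by allocated arm. No rule for moving anyone between groups is given. This stands: regrouping is a literal reading, not a documented procedure. It does not rescue the text, because the label would then misname the primary analysis, and exclusion after randomisation would remain.

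Four stronger inferences are tempting, and the document does not support them.

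- **Rare attenders will be dropped or counted as untreated.** The plan accepts one to five therapy days a week as the natural dose, and attendance frequency is only an exploratory subgroup.
- **The result is biased towards MAKS.** The document does not say who declines or how many. The direction rests on decliners having a worse prognosis, which is plausible but assumed.
- **The large bias figures describe this trial.** They need both regrouping and high assumed refusal. If the planned regression adjusts for baseline score, which is not stated, part of the prognostic gap would be absorbed.
- **Caregiver follow-up ends when the user leaves.** Interviews are scheduled to 24 months and nothing stops them at that point.

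Two further defences have limited force. The phrase about primary outcome variables may have been meant for user outcomes only, but no other strategy is given for caregivers. Burden of care may lose its object after a death, but that does not affect WHO-5 or caregivers of living users.

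**Conclusion.** The point holds in conditional form. The article makes as treated its primary strategy, leaves it undefined, and names no analysis of the primary outcomes by randomised arm. Taken literally, this gives up the randomised comparison. Taken as completers by allocated arm, it is mislabelled and still weakened by exclusions after randomisation. Under either reading the stated reason does not justify the choice, and for BSFC-s and WHO-5 it does not apply at all.

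Confidence is high on the label and on the mismatch with the caregiver outcomes, and moderate on whether anyone would be regrouped and in which direction bias would run. The illustrated sizes, about 0.01 SD with 5% type I error up to 0.17 SD with 27%, rest wholly on the assumed refusal rates and prognosis. The conclusion does not depend on them.

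**What to change.** In the Data analysis section:

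1. Make the primary analysis of ETAM, MMSE, BSFC-s and WHO-5 by the centre's randomised arm, regardless of MAKS participation.
2. Include all enrolled dyads with any available data under a stated missing-data method, such as a likelihood-based mixed model or multiple imputation, and add a sensitivity analysis for users lost to death or nursing home.
3. Remove the drop-out rationale for the caregiver outcomes.
4. Define as treated and keep it as a labelled secondary analysis.

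The cost is wording and one sensitivity analysis. No new data collection is needed, since caregiver follow-up is already scheduled. The downside is that the estimated effect may be somewhat smaller.
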